### Primary outcome measures

#### Patient-centered outcomes

The primary patient-centered outcomes include the Visual Analog Scale (VAS) for LBP, the 24-item RMDQ, and the Patient Reported Outcomes Measurement Information System (PROMIS)-29 questionnaire. The RMDQ has been validated in previous studies in patients with LBP and is more responsive to change over time than most other functional status measures
[52–54]. The VAS is used to evaluate the worst, least, and average LBP over the past 24 hours using a 100 millimeter horizontal scale (0 = no pain; 100 = worst imaginable pain). Current pain is also monitored with the VAS at the beginning and end of each TV. The VAS has excellent metric properties, is easy to administer and score, and has received much use in LBP research
[11]. The comprehensive LBP status is evaluated using the PROMIS-29 questionnaire, which is a collection of questions measuring physical function, anxiety, depression, fatigue, sleep disturbance, satisfaction with social role, pain interference and pain intensity. It aims to provide clinicians and researchers access to efficient, precise, valid, and responsive adult- and child-reported measures of health and well-being
[55]. Biomechanical assessors and treating clinicians are blinded to patient-centered outcomes data.

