#### Posterior-anterior stiffness of the lumbar spine

Lumbar spine stiffness is assessed sequentially with three approaches using hand palpation, a hand-held instrumented device, and an automated device, respectively. The hand-held instrument approach is the primary measure as it has been validated by our study team and demonstrated good reliability (0.79)
[56, 57]. The same set-up allows us to implement hand palpation in a manner that mimics spinal stiffness assessments in clinical practice and will allow us to explore the association between stiffness as measured by palpation versus the hand-held instrument. Because the hand palpation approach was thought to be less intrusive, it is tested before the hand-held approach in the trial. As we finalized the protocol for study launch, a study using an automated stiffness assessment method with high within- and between-day reliabilities (0.99 and 0.98) was published and suggests that spinal stiffness may have important clinical implications
[23]. We contacted the authors who loaned us the equipment for use as an added stiffness measure. However, due to the study timeline, and technical and training requirements, the automated stiffness procedure was not implemented until the clinical trial enrolled 20 participants.

During stiffness assessments, participants lie prone while study clinicians mark the skin with a sterile surgical marking pen at the following locations: posterior superior iliac spines, spinous processes the seventh cervical vertebra (C7), the eleventh thoracic vertebra (T11) to the fifth lumbar vertebra (L5), interspinous spaces from T10 to the first level of sacrum (S1), and the most concave lumbar segment while lying prone (Figure 

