1A). During the hand palpation assessment, the participants lie face down on a custom-made chiropractic treatment table with force plates (Model 4060-NC, Bertec Inc., Columbus, OH) embedded under the cushions that support the thoracic and pelvic regions and acquire the palpatory force transmitted through the participant. The clinician applies a gentle anteriorly directed force consistent with the level typically used during examination to the vertebral levels L1 to L5. An infrared smart marker (Optotrak 3020/Certus hybrid system, Northern Digital Inc., Waterloo, Ontario, Canada) is placed on the clinician’s palpatory hand to simultaneously acquire displacement. The sampling rate for the Optotrak system is set at 100 Hz while the sampling rate for the force plates is set at 1000 Hz. No specific instruction is given to participants in terms of their breathing during the test. Figure 1B demonstrates the setup for the palpatory stiffness measurement.

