The hand-held stiffness device consists of a force transducer (Model # LC201-50, Omegadyne Inc., Sunbury, OH) and infrared smart markers for accurate force and displacement measurement. The assessment is performed with the participant lying prone on the treatment table. The examiner assesses tolerance of participants by pressing gradually up to a maximum of 80 N with the stiffness device in an anterior direction over the pre-marked spinous process of each lumbar vertebra from L1-L5. Participants inform the examiner if the pressure causes discomfort. When the maximum pressure of 80 N is reached an audible tone sounds as feedback to the examiner to stop compressing and withdraw the device. If pressure from the stiffness device causes discomfort, the test is reapplied more slowly and the participant indicates the level of pressure causing discomfort. If the tolerance test does not cause discomfort with 80 N of pressure at any vertebral level, the subsequent stiffness tests are conducted with a maximum pressure of 80 N. If the participant indicates discomfort during the tolerance test, the subsequent stiffness test is conducted at all vertebral levels using a maximum force value 10 N lower than the lowest value causing discomfort at any vertebral level during the tolerance test. If tolerance to the hand-held stiffness device is less than 60 N at any vertebral level, the hand-held stiffness test, as well as the automated stiffness test, is not performed. Both force and displacement are recorded using a Motion Monitor data acquisition workstation (Innovative Sport Training, Chicago, IL) at a sampling rate of 1000 Hz. The stiffness measures are performed by pressing anteriorly over each lumbar spinous process for 5 cycles at a rate of approximately 1 repetition per second. The participants are instructed to make a deep breath in, a deep breath out, and then inhale half way and hold their breath during which the test is performed. The average stiffness obtained over the last 4 cycles is used for analysis. Figure 
1C demonstrates the setup for the hand-held stiffness measurement.

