### Statistical analysis

SAS System for Windows and R (http://www.r-project.org/) will be used for data analysis. Descriptive statistics of participant baseline characteristics and all measurements for each of the 3 assessment times will be calculated. The 3 different methods of collecting spinal stiffness will be compared with intraclass correlation coefficients. The general approach to data analysis will be to first summarize the variations in the physiological and kinetic measures using hierarchical linear regression models and then to use that information to determine the most appropriate statistical methods, including linear mixed regression models
[65] and conditional linear mixed regression models
[65, 66].

For Specific Aim 1, the variations in physiological measures will be summarized using a hierarchical linear regression model with a random effect for participant. If there is a non-significant random effect for participant, then this estimated random effect will be considered a sufficient summary of the physiological measures over time and linear mixed regression models will be used to examine the association between that random effect and the patient-centered outcome variables. If there is a significant random effect for participant, then there is variation in the measures over time. In this case, a linear mixed regression model with time-varying covariates will be fit to assess the association between the physiological measurements at a particular time point and patient-centered outcomes at the subsequent visit(s).

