For Specific Aim 2, the variations in kinetic measures will be summarized using a hierarchical linear regression model with random effects for clinician and for participant nested within clinician. Intraclass correlation coefficients will be computed to establish if there is substantial consistency within clinician within participants and within clinician across participants and if there is sufficient variation between clinicians to allow evaluation of how variations in kinetic measures can predict patient-centered outcomes. If the random effect for participant within clinician is non-significant, or the intraclass correlation coefficient is 0.7 or higher, then the estimated random effect for clinician will be considered a sufficient summary of the delivery of care by an individual clinician. In this case, the association between this random effect and patient-centered outcomes will be evaluated using a linear mixed regression model. If there is not sufficient consistency within clinician between patients, but there is consistency within a clinician within participants, it will indicate that clinicians vary their care by participant but provide a consistent level of care across the course of treatment. In this case, the linear mixed regression model will be used to estimate the association between random effects specific to the clinician/participant combination and patient-centered outcomes. If consistency within clinicians and within participants cannot be established, this indicates substantial variation in the care provided across time by clinicians within a participant. In this case, we will fit a linear mixed regression model with time-varying covariates to assess the association between the kinetic measurements at a particular time point and patient-centered outcomes at the subsequent visit(s).

In the analysis for both specific aims 1 and 2, the complexity introduced by modeling with time-varying covariates may be better served with conditional linear mixed models. Regardless of what model is chosen, alternative models will be fit to assess the sensitivity of the statistical model to any assumptions about consistency.

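### The Aim 1 model for the physiological measures has no assessor term; if more than one person takes the palpation or hand-held stiffness readings, assessor differences are counted as participant or residual variance

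*Protocol article*

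**What the plan says.** In the Statistical analysis section, the Aim 1 paragraph specifies that "the variations in physiological measures will be summarized using a hierarchical linear regression model with a random effect for participant". That model then feeds the models linking physiology to patient-centered outcomes. The Aim 2 paragraph, on kinetic measures, uses a "hierarchical linear regression model with random effects for clinician and for participant nested within clinician". A closing sentence promises alternative models to test assumptions about consistency; it does not mention assessors.

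On who takes the readings, the article gives only hints. The Patient-centered outcomes section says "Biomechanical assessors and treating clinicians are blinded to patient-centered outcomes data". The stiffness section says "participants lie prone while study clinicians mark the skin with a sterile surgical marking pen". For palpation, "The clinician applies a gentle anteriorly directed force consistent with the level typically used during examination". For the hand-held device, the examiner works by "pressing anteriorly over each lumbar spinous process for 5 cycles at a rate of approximately 1 repetition per second". The same section names the hand-held device as the primary stiffness measure and quotes a reliability of 0.79, without saying whether this is within or between examiners. Nowhere does the article say how many people perform each test, or whether one person follows a participant through all visits.

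**The concern.** Aim 1 exists to supply variability and effect-size figures for planning later trials (end of the Background). A source of variance that belongs to the operator rather than the patient should be kept apart from those figures.

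Palpation has no target force. The hand-held device is driven by hand at an approximate rate, over landmarks that a clinician has marked. A user also picks the two force points between which the slope is fitted. Each step lets one operator read systematically higher or lower than another.

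If several people take the same reading and the model knows only participants, later trials would be planned on a participant or residual variance that contains operator differences, and on an association weakened by them.

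**Working it through.** The article has no variance figure or power calculation to reproduce, so this check shows where an omitted assessor effect goes and how large it could be under stated assumptions.

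**Inputs from the article:** 80 participants (Sample size); six sets of physiological readings each, before and after treatment at three visits (Patient visit protocol); reliability 0.79 for the hand-held device.

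**Assumed:** 0.79 is read as an intraclass correlation, so participant variance is 0.79 and residual variance 0.21. There are k = 4 assessors with variance v = 0.10 (range 0.05 to 0.20), added on top. Each reading is participant + assessor + residual, analysed by a one-way random-effects model for participant only. With k assessors allocated at random, the expected assessor variance realised in the sample is s = v(k − 1)/k = 0.75v, which is 0.0375, 0.075 and 0.15.

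**(a) One assessor follows each participant.** All of s enters the participant component:
- participant variance = 0.79 + s = 0.83, 0.87, 0.94 (true 0.79)
- residual = 0.21, unchanged

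**(b) Assessors rotate at random between visits, with the same person before and after treatment.** The six readings form three pairs sharing an assessor. The pooled within-participant variance gains 4s/5 = 0.8s. The participant component gains s/3 − 0.8s/6 = 0.2s:
- residual = 0.21 + 0.8s = 0.24, 0.27, 0.33 (true 0.21)
- participant variance = 0.79 + 0.2s = 0.80, 0.81, 0.82

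Simulation agrees with these formulas to within 0.01. At v = 0.10 it gave 0.866 and 0.211 in case (a), and 0.806 and 0.270 in case (b). With k = 1 or v = 0 the estimates stay at about 0.79 and 0.21.

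**Association.** Take a true correlation of 0.40 with an outcome, using the mean of the six readings. The residual then contributes 0.21/6 = 0.035.
- No assessor effect: 0.40 × √(0.79/0.825) = 0.391
- Case (a): 0.40 × √(0.79/(0.825 + s)) = 0.383, 0.375, 0.360
- Case (b): 0.40 × √(0.79/(0.825 + s/3)) = 0.388, 0.386, 0.380

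**A less reliable measure.** Assume participant share 0.50, three readings, three assessors, and an assessor share of 0.10 to 0.30 with residual 0.40 to 0.20. Here s = (2/3)v.
- One assessor per participant: participant variance is 0.50 + s = 0.57 to 0.70. The correlation is 0.40 × √(0.50/0.70) = 0.338 at the low end and 0.40 × √(0.50/0.767) = 0.323 at the high end, against 0.355 and 0.376 with the assessor effect removed.
- Rotating: the residual is 0.40 + 0.067 = 0.47 down to 0.20 + 0.20 = 0.40.

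**Against sampling error (first set of assumptions).**
- Standard error of the participant variance: √(2/79) × 0.825 = 0.13, so the excess of 0.075 in case (a) is under one standard error.
- Standard error of the residual: √(2/400) × 0.21 = 0.015, so the excess of 0.06 in case (b) is about four standard errors.
- Standard error of the correlation: (1 − 0.16)/√79 = 0.09, several times the attenuation.

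**Mean change over time.** Random rotation produces little: at v = 0.10 the simulated mean absolute change between first and last assessment visits was 0.054, against 0.04 from noise alone. Only a wholesale change of assessor before the last visit creates a sizeable false change, about √(2v) × √(2/π) = 0.36 standard deviations (0.25 to 0.50).

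**The case against.** The strongest objection is to the premise. The plural for assessors comes from a blinding sentence that covers four different tests, so it fits one person per test. The plural for clinicians concerns skin marking, not the readings. Palpation and the hand-held test are described with a single clinician or examiner. This stands: more than one assessor per reading is an inference, and the point must be conditional.

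Second, the article has safeguards. Every stiffness test uses the slope over the same 10 N to 60 N window, so a heavier hand does not directly raise the result. The hand-held test has a force ceiling with an audible signal, a breathing instruction, and averaging of the last four cycles. The formulas for the two relative stiffness measures, GSV and nGSV, are not shown. If they measure spread across levels, a shared assessor offset cancels in the first and a shared scaling in the second. These features damp operator effects, but they do not remove differences in contact point, rate or landmark placement.

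Third, an assessor term may be set in a full protocol or analysis plan that is not shown. That is possible. But the article does state the Aim 1 random-effects structure, and the comment is on that structure.

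Three stronger readings are tempting and are not supported:
- That Aim 1 contradicts Aim 2. In Aim 2 the "random effects for clinician and for participant nested within clinician" describe how treatment is delivered, which is what that aim studies. They are not measurement-error terms.
- That assessor differences will pass for change over the course of treatment. This needs assessor turnover aligned with visit, of which the article shows no sign.
- That the choice between the two Aim 1 models would flip because assessor variance makes the participant effect significant. Under the first set of assumptions the expected mean-square ratio is already (6 × 0.79 + 0.21)/0.21 = 23.6 without any assessor effect.

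**Conclusion.** The point holds in conditional form. The stated Aim 1 model cannot separate assessor from participant or residual variance. This matters for palpation and hand-held stiffness if more than one person takes them. It is weaker for the flexion-relaxation ratio, which is computed within one recording with only the region limits open to user adjustment. It is slight for the automated test, where an actuator applies the load.

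Under the first set of assumptions, participant variance is overstated by about 5% to 19% (0.0375/0.79 to 0.15/0.79) with a constant assessor, or the residual by about 14% to 57% (0.03/0.21 to 0.12/0.21) with rotation. The loss of correlation is modest, at most 0.03 there and about 0.05 in the less reliable case. The variability estimates are therefore more at risk than the association.

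All these sizes rest on assumed numbers of assessors and assumed assessor variances. If 0.79 is a between-examiner figure, the assessor share for the hand-held device cannot exceed 1 − 0.79 = 0.21. With one assessor per test the effect is nil. This is an improvement worth making, not a flaw that undermines the study.

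**What to change.** State how many people perform each test and how they are allocated to participants and visits. Keep an assessor ID with every palpation and hand-held stiffness record. For either measure, if more than one person takes it, add an assessor term to the Aim 1 model: fixed if assessors are few, otherwise random. Report its contribution, and use assessor-adjusted values in the association models. For the flexion-relaxation ratio, do the same only as a sensitivity analysis, using the ID of the person who set the regions. The automated test needs no such term. Where one person takes all readings of a measure, say so and omit the term.

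The cost is one sentence in the analysis plan, one model term and one ID field, which is easiest to secure while the visit records are still traceable. Statistically it uses a few degrees of freedom, and with few assessors their variance will be imprecisely estimated. If assessors turn out to have changed in step with the visits, the term cannot fully separate assessor from time, and that should be reported as a limitation.

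### The Specific Aim 1 model-selection rule is inverted: it keeps the participant effect as predictor when that effect is least informative, and reads stable differences between participants as change over time

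*Protocol article*

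**What the plan says.** In the Statistical analysis section of the protocol article, the Specific Aim 1 paragraph summarises the physiological measures with a "hierarchical linear regression model with a random effect for participant". No random slope and no visit-level component is named. Two branches follow.

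- **Not significant:** "If there is a non-significant random effect for participant, then this estimated random effect will be considered a sufficient summary of the physiological measures". Then "linear mixed regression models will be used to examine the association between that random effect and the patient-centered outcome variables".
- **Significant:** "If there is a significant random effect for participant, then there is variation in the measures over time". Then "a linear mixed regression model with time-varying covariates will be fit to assess the association between the physiological measurements at a particular time point"; the outcomes are those of later visits.

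The Specific Aim 2 paragraph uses a nested model, with participant within clinician. "If the random effect for participant within clinician is non-significant, or the intraclass correlation coefficient is 0.7 or higher", the clinician effect, one level up, is taken as the summary. Time-varying covariates come in only when consistency within clinicians and within participants cannot be shown. The same section says that conditional linear mixed models may serve better for both aims, and that alternative models will be fitted to check sensitivity to the consistency assumptions.

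**The concern.** In repeated measurements a participant random effect is the part of the measure that stays with the person. If it is significant, people differ from each other in a lasting way. That says nothing about whether anyone changes. Change sits in a visit effect, a random slope or the within-participant variance, and the Aim 1 rule tests none of these.

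If the participant effect is not significant, no lasting differences have been detected and the estimated effects are pulled towards zero. The rule takes them as predictor in exactly that case. When the measure is a stable trait, so that one value per person is a good summary, the rule turns to time-varying covariates instead.

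The primary objective is to obtain preliminary estimates of variability and effect size for these associations, for planning later trials. The Background section separates baseline prediction of improvement from change along the course of treatment. This rule confuses the two.

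**Working it through.** The protocol gives no figure for this rule, so there is none to reproduce. The check asks which branch the rule picks for measures of differing stability.

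**Inputs**
- n = 80 participants (Sample size).
- k = 6 assessments, before and after treatment at three visits (Patient visit protocol); k = 3 if only one reading per visit is used.
- Test level 0.05: an assumption, as none is stated for this test.
- Participant ICC: an assumption, taken from 0 to 0.79. The top value borrows the hand-held device's reliability ("demonstrated good reliability (0.79"). The type of that reliability is not stated, so it is illustrative only.
- One-way random-intercept model with balanced data and exchangeable readings.

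**Formulas**
- F = MS between / MS within, with n − 1 and n(k − 1) degrees of freedom: 79 and 400 for k = 6; 79 and 160 for k = 3.
- P(non-significant) = P(F < Fcrit / R), where R = 1 + k·ICC/(1 − ICC).
- Reliability of the participant effect = k·ICC / (1 + (k − 1)·ICC).
- The variance estimate is zero when MS between ≤ MS within.

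Fcrit is 1.312 for k = 6 and 1.365 for k = 3.

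**Example, ICC 0.30, k = 6:** R = 1 + 6 × 0.30/0.70 = 3.571; 1.312/3.571 = 0.367; P(F < 0.367) ≈ 2 × 10⁻⁷. For k = 3: R = 2.286; 1.365/2.286 = 0.597; P ≈ 0.006.

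| Participant ICC | P(summary branch), k = 6 | P(summary branch), k = 3 | Reliability of participant effect, k = 6 |
|---|---|---|---|
| 0 | 0.95 | 0.95 | 0 |
| 0.10 | 0.10 | 0.56 | 0.40 |
| 0.30 | about 2 × 10⁻⁷ | 0.006 | 0.72 |
| 0.79 | about 10⁻³³ | practically 0 | 0.96 |

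The more reliable the participant effect, the less likely the rule is to use it.

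**Inside the summary branch at ICC 0.** P(F < 1) is 0.52 for k = 6 and 0.51 for k = 3. In about half of all such datasets the variance estimate is therefore zero, every participant effect is 0, and no association can be estimated. As a share of the datasets that enter the branch, this is about 0.52/0.95 = 54% and 0.51/0.95 = 54%.

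A simulation of 4,000 replicates per setting agrees. At ICC 0.79 the effect was significant in 100% of replicates, although the simulated participants had no systematic change over time. At ICC 0 and k = 6 it was non-significant in about 95%, and the estimated effects in those replicates had a mean SD of 0.02 against a total SD of 1.

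**Aim 1 beside Aim 2.** In Aim 2 the effect tested (participant within clinician) and the effect kept (clinician) sit at different levels, so a null lower-level effect can justify summarising at the level above. In Aim 1 there is only one level, so the effect tested and the effect kept are the same. In Aim 2 consistency leads to a summary; in Aim 1 strong consistency within a person leads to time-varying covariates.

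**The case against.** **The random effect may mean a random time slope.** The sentence on significance could then stand, since significant slope variance means that people change differently. The other sentence could not, because slopes not distinguishable from zero would become the sufficient summary. No slope is named, and no single meaning makes both sentences true.

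**The time-varying model is still usable.** This stands. At ICC 0.30 or more the rule practically always leads to a model that relates a measurement at one visit to later outcomes. That model can be fitted and does not need a time trend. A reader might infer that whichever branch is taken the estimates are wrong; the documents do not support that.

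**Shrinkage alone does no harm.** This also stands. At the edge of significance with k = 6 the effects keep only 1 − 1/1.312 = 24% of their size. With balanced data, though, every participant is scaled by the same constant, which rescales the coefficient and leaves the correlation and test statistic unchanged. A reader might infer that a non-significant effect can predict nothing. That holds only when the variance estimate is exactly zero; otherwise the predictor is noisy.

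**An ICC of 0 is not expected.** The Data reduction text on stiffness allows for participants who are stiffer or more flexible overall. That concerns raw stiffness, and the derived variation indices could be less stable. The documents do not settle which ICC applies, so the range is shown.

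**Other text softens the rule.** The promised alternative models mean that reported results need not hang on one branch. They do not correct the rule or its stated interpretation.

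**Conclusion.** The rule is wrong as written. It picks the participant effect as predictor where it is least informative, passes it over where it is reliable, and describes lasting differences between people as change over time. It also conflicts with the consistency logic of Aim 2 in the next paragraph.

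The direction of the error follows from what a random effect is and needs no assumption. Its size rests on the 5% level, the one-way balanced model and the assumed ICC range. Real data with dropout, or pre- and post-treatment readings that differ systematically, would shift the figures but not the pattern.

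The harm is limited to a wrong branch and a false interpretation. The study is observational and seeks preliminary estimates, so no confirmatory test is at stake. Because those estimates are its main product and are meant for planning later trials, the rule should still be corrected before analysis.

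**What to change.** Rewrite the Specific Aim 1 rule on the consistency criterion that Aim 2 already uses.

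1. Estimate the participant ICC for each physiological measure from between- and within-participant variance, with visit and pre/post as fixed effects.
2. If the ICC is high (for example the 0.7 used in Aim 2), use the participant-level value as predictor of outcome.
3. Otherwise use the time-varying model, with each participant's mean entered separately from the deviation around it.
4. Delete the sentence that equates a significant participant effect with variation over time.

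Swapping the two branches is not enough, because a test of between-participant variance does not measure change over time. The planned sensitivity models can stay as they are. The cost is rewording and slightly more analysis, with the same data and software.

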**Discussion:**

Beside alterations in material properties of the passive components of the spine, increased neuromuscular activity may also contribute to a stiffened spine. Examining changes in both spinal stiffness and flexion-relaxation along the course of the treatment provides an opportunity to understand if the therapeutic effect of SM is associated with its action on active and/or passive components of the spine.

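### The time-varying models for Aims 1 and 2 yield one coefficient that blends level and change; it needs splitting before it supports statements about change or plans later trials

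*Protocol article*

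**What the plan says.** In Statistical analysis, Aim 1 starts with a hierarchical model that has a participant random effect. If that effect is significant, "a linear mixed regression model with time-varying covariates will be fit to assess the association between the physiological measurements at a particular time point" and the patient-centred outcomes at the visit or visits that follow. The branch is justified thus: "If there is a significant random effect for participant, then there is variation in the measures over time".

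Aim 2 has a parallel branch, used when care is not consistent within clinicians and participants: "we will fit a linear mixed regression model with time-varying covariates to assess the association between the kinetic measurements at a particular time point" and later outcomes.

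Neither description separates a participant's usual level from the departures around it. Conditional linear mixed models are listed among the candidate methods. For both aims the plan then says only that "the complexity introduced by modeling with time-varying covariates may be better served with conditional linear mixed models". It also promises alternative models, to test assumptions about consistency.

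The interpretation that depends on change is in the Discussion part of the Abstract: "Examining changes in both spinal stiffness and flexion-relaxation along the course of the treatment provides an opportunity to understand if the therapeutic effect" of manipulation is tied to its action on the spine. The Background adds that the estimates will help plan trials on baseline association, prediction of improvement, and improvement of the measures during treatment.

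**The concern.** Whether changes in stiffness or flexion-relaxation go with the treatment effect is a within-person question. A measurement entered as one covariate in a random-intercept model gives one slope. That slope is a weighted average of a between-person slope (stiffer people have worse scores) and a within-person slope (when a person's stiffness falls, the score falls).

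Two errors can follow. A purely cross-sectional association may be presented as a link between physiological change and improvement. A real change effect may be diluted by an absent or opposite level association. In either case the effect size passed to later trials answers neither question cleanly.

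The Aim 1 trigger adds to the problem. A significant participant random effect shows stable differences between people, so the branch is entered exactly when between-person variance is evident.

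**Working it through.** **Inputs from the protocol.** Minimum 80 participants (Sample size). Physiology at TV1, TV5 and TV12; outcomes at BL1, TV6 and TV13 (Patient visit protocol), so the closest pairs are TV5 with TV6 and TV12 with TV13. Reliability is 0.79 for the hand-held device and 0.98 between days for the automated device (Posterior-anterior stiffness). The protocol gives no coefficient, power or error rate for this model and no inputs behind the 80, so there is no figure of its own to reproduce.

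**Assumptions.** The measure's ICC over treatment (rx), the outcome's residual ICC (ry) and the person-level correlation are not in the protocol. The reliabilities serve only as stand-ins for rx. Measure and outcome variances are set to 1 before any within-person effect is added.

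**Step 1: between-person share.** With m paired visits, share = B/(B+W), where B = (1+(m−1)rx)/(1+(m−1)ry) and W = (m−1)(1−rx)/(1−ry). For m = 2:

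| rx | ry | B | W | Share |
|---|---|---|---|---|
| 0.98 | 0.3 | 1.98/1.3 = 1.523 | 0.02/0.7 = 0.029 | 98% |
| 0.98 | 0.6 | 1.98/1.6 = 1.238 | 0.02/0.4 = 0.050 | 96% |
| 0.79 | 0.6 | 1.79/1.6 = 1.119 | 0.21/0.4 = 0.525 | 68% |
| 0.79 | 0.8 | 1.79/1.8 = 0.994 | 0.21/0.2 = 1.050 | 49% |
| 0.5 | 0.6 | 1.5/1.6 = 0.938 | 0.5/0.4 = 1.250 | 43% |
| 0.3 | 0.8 | 1.3/1.8 = 0.722 | 0.7/0.2 = 3.500 | 17% |

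With two visits the share exceeds one half only when rx exceeds ry.

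**Step 2: coefficient when change is unrelated to outcome.** Take rx = 0.79, ry = 0.6, person-level correlation 0.3. Person-level covariance = 0.3 × √(0.79 × 0.6) = 0.2065. Variance of a two-visit mean = (1 + 0.79)/2 = 0.895. Between-person slope = 0.2065/0.895 = 0.231. Single coefficient = 0.681 × 0.231 + 0.319 × 0 = 0.157. The simulated mean was also 0.157.

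**Step 3: how often it looks non-zero.** Simulations used 80 participants, two visits, ry = 0.6, within-person slope zero, and 800 or 1,000 replicates per cell. Ranges are over repeated runs. Share of trials with two-sided p < 0.05:

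| rx | correlation 0.3 | correlation 0.5 |
|---|---|---|
| 0.5 | 23–29% | 61% |
| 0.79 | 44–49% | 90% |
| 0.98 | 60–67% | 98% |

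With correlation 0 the rate is 5–6%. Three paired visits at correlation 0.3 give 20%, 41% and 68% for the three values of rx. Adjusting for the baseline outcome at rx = 0.79 and correlation 0.3 lowers the rate to 20–21%. The deviation-from-mean term stays at about 3–7% throughout.

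**Step 4: a real change effect.** With rx = 0.79, within-person slope 0.5 and no person-level link, the within-person part also enters the person means: 0.5 × (0.21/2)/0.895 = 0.059. Single coefficient = 0.681 × 0.059 + 0.319 × 0.5 = 0.20. Simulation gave 0.20–0.21 with 58–61% power; the split gave 0.50–0.51 with 88–91%. With slope −0.5 and person-level correlation +0.3, the single coefficient is 0.681 × (0.231 − 0.059) − 0.319 × 0.5 = −0.04, so the effect almost vanishes.

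**Step 5: which split.** Suppose TV1 is used as the reference instead of the mean. Given the TV1 value, a later value has variance 1 − 0.79² = 0.376, and two later values have covariance 0.79 − 0.79² = 0.166. The remaining ICC is 0.441, so B = 1.441/1.6 = 0.901, W = 0.559/0.4 = 1.397, and the share is 0.392.

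- Step 2 case: 0.392 × 0.2065 × 0.21/0.271 = 0.063 leaks through, where 0.271 = (0.376 + 0.166)/2. Simulated rejection is 9–11% for rx of 0.5 to 0.79.
- True slope 0.5: 0.392 × (0.5 × 0.105/0.271) + 0.608 × 0.5 = 0.38.

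Deviation from the mean has neither fault.

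**The case against.** The case on the other side is substantial.

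- **Centring is detail for an analysis plan that is not shown.** Partly right: silence alone would not be a point. But the article does describe the covariate as the measurement at a time point, makes the within-person alternative discretionary, and misreads its own trigger.
- **The within-person tool is already named.** True, and it narrows the point. It remains optional, is justified by complexity, and has no rule for when it applies or which estimate supports a statement about change. Used alone, it would discard the level association needed for the baseline question.
- **The model describes level, and Aim 1 is estimation.** This stands. No alpha or success rule is attached, and no sentence says this coefficient will be reported as evidence on change. The percentages above are therefore not type I error rates of a planned test. Where a person-level link exists, a non-zero coefficient is a true association of level. They show only how easily the coefficient could be misread as change.
- **The share is unknown.** This also stands. The reliabilities are not ICCs over six weeks of treatment, and the 0.98 comes from another study. None is stated for flexion-relaxation or for the global stiffness variation measures planned for analysis, one of which is normalised to account for differences between participants. The Aim 2 branch is entered when within-participant variation is large, so its mix may lean within-person.

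**Conclusion.** The point holds as a weakness in what is estimated, and it should be changed. As described, both time-varying models give a coefficient that blends level and change in unknown proportion. Under the stated assumptions it can be clearly non-zero when change is unrelated to outcome (mean 0.157 at measure ICC 0.79, outcome ICC 0.6 and correlation 0.3), or cut a true within-person slope of 0.5 to about 0.20. The problem does not need a between-person majority: at measure ICC 0.5 the share is 43%, and the coefficient is still nominally significant in 23–29% of trials at correlation 0.3.

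A reader might infer that the coefficient is mostly between-person, that a planned test has an inflated false-positive rate, or that the sign would be reversed. The documents support none of these. The ICCs are not given, Aim 1 plans no test, and no scenario examined reversed the sign. The harm arises only if the blended estimate is used for the Abstract's statement about changes or to plan later trials.

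**What to change.** In the time-varying models for both aims:

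1. Replace the single covariate with two terms, the participant's mean over the visits used and each visit's deviation from that mean. Do not use deviation from TV1. Add a visit term.
2. Report both coefficients. Use only the within-person one for statements about change during treatment or visit-to-visit dose-response, and the between-person one for association of level.
3. Keep the conditional linear mixed model as a check on the within-person estimate.
4. Correct the Aim 1 sentence on the random effect: a significant participant effect shows stable differences between people, not variation over time.

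The change is to wording only and needs no new data. It costs one more coefficient per model and a wider within-person interval, especially for the automated device if little of its variance is within person. That width reflects what the study can say about change.
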